## Abstract

**Background:**

Survivors of adolescent and young adult (AYA) cancer (ages 15‐39 y at diagnosis) face persistent psychosocial challenges, including isolation from peers, identity disruption, and unmet supportive care needs. Approximately 90,000 AYAs are diagnosed with cancer annually in the United States, and 86% survive at least 5 years. However, few age-appropriate, scalable, and developmentally tailored online psychosocial interventions exist for this population. Expressive writing (EW) shows promise for improving psychological well-being in survivors of AYA cancer, but traditional individual approaches do not address the preference of AYAs for peer support. A virtual, group-based EW intervention combining private emotional processing with facilitated peer discussion may address multiple unmet needs.

**Objective:**

The primary objective is to evaluate the feasibility and acceptability of a virtual, group-based EW intervention tailored for survivors of AYA cancer. Secondary objectives are to explore preliminary changes in quality of life and psychosocial outcomes, including perceived stress, coping self-efficacy, cancer-related intrusive thoughts, self-compassion, and posttraumatic growth.

**Methods:**

This single-arm feasibility study enrolls 30 survivors of AYA cancer who were diagnosed at ages 15 to 39 years; are 18 to 39 years old at study entry; are 1 to 5 years postdiagnosis; can speak, read, and write in English; and have regular internet access. Participants are assigned to 1 of 3 groups of 10 on the basis of developmental-stage preferences: emerging adults (18‐25 y), young adults (26‐39 y), or a mixed-age group (18‐39 y). The 8-week intervention consists of 4 private writing sessions of 20 minutes each (odd-numbered weeks), alternating with 4 facilitated group discussions on a closed Facebook platform (even-numbered weeks). All procedures are conducted online, with questionnaires and private writings delivered via REDCap (Research Electronic Data Capture). Primary outcomes include feasibility (success criteria: ≥75% of participants complete assessments; ≥75% complete ≥1 private writing sessions; ≥70% complete all private writing sessions; ≥75% complete ≥1 group discussions; ≥70% complete all group discussions) and acceptability (success criterion: mean score ≥3 on a 0‐4 scale). Secondary and exploratory outcomes are assessed at baseline and at 1-month and 3-month follow-ups. Qualitative data are collected through semistructured interviews, open-ended responses, private essays, and group posts or comments and analyzed using the constant comparative method.

**Results:**

This study was funded in September 2024. Recruitment was completed between June 25 and July 7, 2025. Participants are currently completing 3-month follow-up assessments. Data management is expected to be completed by May 2026, and the results will be submitted for publication by the end of 2026.

**Conclusions:**

This study provides critical feasibility and acceptability data for the first developmentally adapted, virtual, group-based EW intervention for survivors of AYA cancer. The findings will inform the optimization and design of a randomized controlled trial to evaluate the intervention’s efficacy in improving outcomes for this population.

## Introduction

### Background and Rationale

Survivors of adolescent and young adult (AYA) cancer (ages 15‐39 y at diagnosis) face distinct psychosocial challenges that persist long after treatment completion. In this protocol, “survivorship” refers to the period beginning at diagnosis and extending through and beyond active treatment [1]. Approximately 90,000 AYAs are diagnosed with cancer annually in the United States [2], and 86% survive at least 5 years [2], resulting in over 2 million survivors of AYA cancer currently living in the United States [3]. During the transition from active treatment to survivorship, AYAs often experience identity disruption and developmental delays [4-6], social isolation from peers [4,6,7], substantial unmet needs for psychosocial support [6,8], and limited access to age-appropriate support services [5,9,10]. These challenges significantly impair quality of life (QOL) [11,12].

The National Cancer Institute (NCI) defines AYAs as individuals aged 15 to 39 years [13], spanning 3 distinct developmental stages: adolescence (15‐17 y, characterized by parental dependence and peer influence), emerging adulthood (18‐25 y, characterized by exploration and transition to independence), and young adulthood (26‐39 y, characterized by established relationships and career development) [14]. Despite these fundamental differences, most research has not stratified outcomes or tailored interventions by developmental stage.

To be most effective, psychosocial interventions for survivors of AYA cancer should be tailored to their preferences. AYAs value convenience and virtual delivery of interventions [15,16], and 95% express willingness to participate in internet-based interventions [17]. As “digital natives” who spend substantial time on social media [18], AYAs also prefer group-based interventions that provide peer support, which is one of their most frequently reported unmet needs [6,19]. A growing body of evidence supports the use of digital psychosocial interventions for cancer survivors broadly. Recent systematic reviews and meta-analyses have demonstrated that digital health interventions, including web-based platforms, mobile applications, and videoconference-delivered programs, can improve QOL, reduce anxiety and depression, and decrease psychological distress in adult cancer populations [20,21]. However, this evidence base is derived predominantly from older adult cancer populations and may not generalize to AYAs, who differ in developmental stage, psychosocial needs, and digital engagement patterns [22].

Among the few digital interventions developed specifically for AYA cancer survivors, peer support has emerged as a promising approach, with recent trials of group online peer support [23], peer mentoring [24], and online group-based cognitive behavioral therapy with peer discussion [25,26] demonstrating preliminary benefits. One psychosocial intervention that can be delivered via the internet and has been studied in cancer survivors is expressive writing (EW). EW, in which individuals are asked to write about their deepest thoughts and feelings [27], has produced improvements in physical and psychological symptoms among older cancer survivors [28]. Two studies showed that EW decreased distress while increasing QOL and coping abilities in AYAs [29,30]. Our team conducted a feasibility study of individual-based EW among 30 AYA cancer survivors who completed weekly writing sessions for 3 weeks. Results showed improvement in QOL (Cohen *d*=0.73) at the 1-month follow-up, with high acceptability [31]. However, in the classic EW paradigm, in which EW is a private exercise focused on disclosing one’s deepest thoughts and feelings about traumatic experiences, a social support component is lacking. Consistent with this limitation, AYAs in our feasibility study expressed a desire to connect with other AYA survivors and share experiences. However, no existing intervention has integrated private EW with facilitated group peer discussion in a single framework. Together, these findings and the broader literature highlighting peer support as a critical unmet need among AYAs motivated the development of the current virtual, group-based intervention that integrates private EW with facilitated peer discussion and has the potential to better align with AYA developmental needs and preferences.

### Conceptual Framework

The intervention design is guided by 2 integrated theoretical frameworks (Figure 1). The private writing component is guided by the self-regulation model [32], which posits that actively inhibiting thoughts and feelings about stressful experiences requires physiological effort that accumulates over time, contributing to chronic stress and adverse health outcomes. Writing about these experiences reduces the cognitive burden of inhibition and facilitates cognitive reappraisal, defined as the process of positively reframing stressors to derive meaning and insight [33]. In the EW part of the intervention, the sequence of writing prompts progresses from emotional disclosure to coping exploration to benefit finding and integration.

**Figure 1. F1:**
[figure not shown]
Conceptual framework for group-based expressive writing intervention.

The group discussion component is guided by self-compassion theory [34], which emphasizes 2 constructs particularly relevant to AYA cancer survivors: common humanity (recognizing shared struggles) and self-kindness (compassionate self-regard). AYA cancer survivors frequently report feeling isolated from same-age peers and disconnected from their precancer identities [4,6], making these constructs particularly relevant to this population. The facilitated peer discussion questions are designed to promote common humanity by encouraging participants to recognize shared experiences, foster self-kindness through supportive and compassionate reflections, and encourage reciprocal peer support while addressing AYA-specific psychosocial challenges.

By combining private self-regulatory writing with facilitated peer discussion designed to cultivate common humanity and self-kindness, this intervention targets both intrapersonal meaning-making and interpersonal support needs. These theoretical foundations directly inform the study objectives: to evaluate whether this integrated approach is feasible and acceptable to AYA survivors (primary aim) and to explore preliminary changes in QOL and psychosocial outcomes consistent with the theoretical frameworks, including perceived stress, coping self-efficacy, intrusive thoughts, self-compassion, and posttraumatic growth (secondary aim). In this paper, we describe the research protocol.

## Methods

This protocol is reported in accordance with the Standard Protocol Items: Recommendations for Interventional Trials (SPIRIT) 2013 guidelines [35]. The completed SPIRIT checklist is provided in Checklist 1.

### Study Design and Setting

This is a single-arm feasibility study without a comparator group and is designed to evaluate the feasibility and acceptability of a virtual, group-based EW intervention for survivors of AYA cancer. The primary objective at this stage is to establish feasibility and acceptability prior to designing a randomized controlled trial. This is an open-label study; no blinding is used, as the single-arm design and behavioral nature of the intervention make blinding of participants or study personnel unnecessary. All procedures are conducted remotely. Surveys and private writing activities are delivered via the secure web-based platform REDCap (Research Electronic Data Capture), and group discussions take place in closed, private Facebook groups.

### Intervention Development

The intervention was developed through an iterative, multistage process. The theoretical foundation drew on the self-regulation model of EW [32] and self-compassion theory [34], as described in the *Introduction*. A targeted literature review identified key features of effective psychosocial interventions for survivors of AYA cancer, including the importance of peer support [6,19], virtual delivery [15,16], and structured writing protocols of sufficient dose and duration [36]. Preliminary research by our team, including a feasibility study of individual-based EW among 30 survivors of AYA cancer [31], provided initial evidence of acceptability and improvement in QOL, while also revealing participants’ desire for peer connection. The iterative development and modification process for the EW intervention is described in detail elsewhere [37].

The initial intervention design was presented to the Young Adult Advisory Council of The University of Texas MD Anderson Cancer Center, which comprised survivors of AYA cancer and providers from the MD Anderson Cancer Center AYA clinic, who provided feedback on acceptability, intervention frequency and duration, writing prompts, and group composition considerations. Specifically, they endorsed the alternating format of private writing followed by group discussion as a way to balance personal reflection with peer interaction. All feedback was systematically reviewed and integrated into the intervention design.

Following this stakeholder engagement, a run-in pilot with 10 survivors of AYA cancer was conducted between January and February 2025 to test logistics and obtain participant feedback. The run-in pilot yielded 2 critical insights that informed the final protocol. First, a group of 5 participants was insufficient to sustain engagement when even 1 or 2 members did not post in a given week. This finding led to the decision to increase the group size to 10 participants, providing a buffer for natural fluctuations in participation while still maintaining a manageable volume of interaction. Second, survivors diagnosed less than 1 year prior struggled with participation due to the demands of intensive treatment and acute adjustment challenges. Time since diagnosis emerged as a more important determinant of feasibility than other clinical factors (such as cancer type, disease status, or treatment status). The eligibility criterion was therefore revised to require that participants be a minimum of 1 year postdiagnosis, reflecting the recognition that different survivorship phases may require different intervention approaches [38,39]. Skill-focused interventions targeting immediate practical concerns may be more appropriate during active treatment [40,41], whereas reflective, meaning-making interventions like this study may be better suited for survivors who are further out from the acute phase of care [42,43]. Additional refinements included improvements to the writing prompt content and facilitated discussion questions based on participant input.

### Participants

Inclusion criteria are age 15 to 39 years at diagnosis; age 18 to 39 years at study entry; 1 to 5 years postdiagnosis (participants may be receiving active treatment, including maintenance therapy, or may be off treatment); ability to speak, read, and write in English; and access to the internet. Exclusion criteria are diagnosis of nonmelanoma skin cancer and any major mental health disorder (eg, schizophrenia or bipolar disorder), as determined by medical records or self-report. Table 1 provides detailed inclusion and exclusion criteria with rationales. The exclusion of individuals with major mental health disorders was implemented for 2 reasons. First, the group-based format of the intervention requires participants to engage in facilitated peer discussion about emotionally sensitive topics, and the presence of acute psychiatric symptoms (eg, psychosis, mania, or active suicidal ideation) could compromise both individual safety and group functioning. Second, the exploratory outcome measures in this pilot study (eg, perceived stress, self-compassion, and posttraumatic growth) could be significantly confounded by concurrent major psychiatric conditions, making it difficult to evaluate preliminary signals of intervention effects. This criterion was determined by clinical judgment at the time of screening rather than by formal diagnostic assessment, consistent with the approach used in similar pilot trials of psychosocial interventions for AYA cancer survivors [23,26].

**Table 1. T1:** Inclusion and exclusion criteria and rationales.

Criterion	Details	Rationale
Inclusion		
Age at diagnosis	15‐39 years	Aligns with National Cancer Institute (NCI) definition of AYAs^a^
Age at study entry	18‐39 years	Participants must be legal adults (≥18 y)
Time since diagnosis	1‐5 years	≥1 year ensures completion of acute treatment and initial adjustment; ≤5 years targets the early survivorship phase
English literacy	Can speak, read, and write in English	Required for current delivery (future iterations will include other languages)
Internet access	Regular access via smartphone, tablet, or computer	Required for virtual intervention; ~97% of US adults aged 18‐39 years have internet access
Exclusion		
Cancer type	Nonmelanoma skin cancer	Has treatment trajectory and psychosocial profile different from those of other cancers
Mental health	Major mental health disorder (eg, schizophrenia or bipolar disorder)	Requires specialized clinical support and could pose safety or feasibility concerns for the intervention

a AYA: adolescent and young adult.

A total sample size of 30 was chosen using a CI approach [44] to provide adequate precision for feasibility metrics. With 30 participants, a 95% CI for a 75% (or 50%) completion rate would have a half-width of approximately 15.5% (or 17.9% in the worst-case scenario), which is acceptable for estimating feasibility [45,46]. This sample size also permits estimation of preliminary effect sizes to inform power calculations for future trials.

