### Group Composition

During the enrollment process, participants indicated their preference for being in a group with participants of a developmentally similar-age group (either 18‐25 y or 26‐39 y), a mixed-age group (18‐39 y), or no preference. This preference-based approach was chosen for 2 reasons. First, the developmental heterogeneity within the AYA age range (spanning late adolescence to early midlife) means that survivors at different life stages may face distinct psychosocial concerns (eg, identity formation and educational disruption for younger AYAs versus career, financial, and parenting concerns for older AYAs) [14]. Allowing participants to self-select into age-based or mixed-age groups reflects the person-centered design principles recommended for AYA intervention research [47]. Second, understanding AYA preferences for group composition is itself a relevant question for intervention optimization, as group cohesion and perceived relevance are known to influence engagement in group-based psychosocial interventions [48]. As an exploratory aim, this study will also examine whether preference-based age group assignment is feasible and whether group composition (younger AYA, older AYA, or mixed-age) is associated with differential patterns of engagement and acceptability.

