#### Primary Outcomes

Feasibility is assessed through prespecified quantitative benchmarks. The criteria for success are as follows: at least 75% of participants complete the 1-month and 3-month follow-up assessments; at least 75% of participants complete at least 1 private writing task and ≥70% complete all 4 writing tasks; and at least 75% of participants complete at least 1 group discussion and ≥70% complete all 4 discussions.

Acceptability is assessed through an acceptability questionnaire containing 9 items rated on a 0 to 4 scale [52], with a mean score of 3 or greater indicating an acceptable intervention. In addition, semistructured postintervention interviews explore participants’ experiences with the intervention format, content, and delivery; group composition; perceived changes in themselves; barriers to participation; and suggestions for improvement.

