### Statistical Analysis

For quantitative data, feasibility metrics are summarized as proportions with 95% CIs. Descriptive statistics (means, medians, and SDs as appropriate) are used to characterize the sample and engagement patterns. For preliminary outcome exploration, mean scores at each time point (baseline, 1 mo, and 3 mo) are reported for each measure. Within-participant changes from baseline to follow-ups are examined using 2-tailed paired *t* tests for approximately normally distributed variables or Wilcoxon signed-rank tests for nonnormal distributions. Effect sizes (Cohen *d*) with 95% CIs are calculated for key outcome changes to aid in planning future studies. All quantitative analyses are considered exploratory rather than confirmatory. Due to the small sample size of the study, our primary analysis for the secondary outcomes will be based on all observed data, with acknowledgment of the limitations of the approach. If, however, the proportion of missing data is excessively high (eg,≥30%), we may explore multiple imputation approaches to handling the missing data, for example, by assuming a missing-at-random mechanism, as part of our sensitivity analyses. No interim analyses or stopping rules are planned for this pilot feasibility study.

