## Results

This study was funded in September 2024. Participant recruitment was completed between June 25, 2025, and July 7, 2025, yielding 30 enrolled participants. All 30 participants were successfully assigned to an intervention group according to the scheme described (2 developmentally stratified groups and 1 mixed-age group). The 8-week intervention phase (private writing and group discussion sessions) was completed by all 3 groups. Follow-up assessments at 3 months after the intervention are currently ongoing. Data processing and management (including quantitative dataset cleaning and qualitative transcription) are expected to be completed by May 2026. The data will be analyzed, and a manuscript on the results and findings is anticipated to be submitted for publication by the end of 2026.

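### The planned precision of 15.5 and 17.9 points assumes 30 independent participants, which is too favourable for the two group-discussion completion criteria

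*Protocol article*

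**What the plan says.** The sample-size paragraph under Participants gives precision as the basis for the number enrolled: "A total sample size of 30 was chosen using a CI approach". It continues that "a 95% CI for a 75% (or 50%) completion rate would have a half-width of approximately 15.5% (or 17.9% in the worst-case scenario" and judges this acceptable for estimating feasibility. It mentions neither groups nor an allowance for correlation.

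The delivery is grouped. The Abstract (Methods) says "Participants are assigned to 1 of 3 groups of 10", and the Results section confirms it: "All 30 participants were successfully assigned to an intervention group". Under Primary Outcomes, two of the success criteria concern the group activity: "at least 75% of participants complete at least 1 group discussion and ≥70% complete all 4 discussions".

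Two passages bear on dependence within groups. Intervention Development reports from the run-in pilot that "a group of 5 participants was insufficient to sustain engagement when even 1 or 2 members did not post in a given week", and gives this as the reason for moving to groups of 10. Group Composition adds that "group cohesion and perceived relevance are known to influence engagement in group-based psychosocial interventions".

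The Statistical Analysis section plans that "feasibility metrics are summarized as proportions with 95% CIs", without reference to group. The Limitations section acknowledges limited power but not clustering.

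**The concern.** A binomial half-width for n = 30 is right when each participant's outcome is independent of the others'. For the discussion criteria the article gives reasons to doubt this. It lets the dependence of engagement on fellow members drive the choice of group size, and then sets total sample size as if there were none. With positive within-group correlation, 30 people in three groups carry less information about the completion rate than 30 independent people, so the interval that honestly describes the uncertainty is wider than planned.

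What is at stake is how firmly the discussion-engagement rates can be carried into the planned randomized trial. Someone designing that trial would read the estimates as good to within about 15.5 to 17.9 points, when for these two criteria the margin may be larger.

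**Working it through.** **Inputs.** From the article: n = 30; three groups, so m = 10 per group; 95% confidence; completion rates of 75% and 50% (Participants) and the 70% benchmark (Primary Outcomes). Not in the article: the ICC. I take 0.02, 0.05 and 0.10 as assumptions to show a range.

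**Step 1: reproduce the stated figures.** The simple (Wald) half-width is 1.96 × √(p(1 − p)/n).
- p = 0.75: 1.96 × √(0.1875/30) = 1.96 × 0.0791 = 0.155
- p = 0.50: 1.96 × √(0.25/30) = 1.96 × 0.0913 = 0.179

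Both match. Other interval types do not match both: Wilson gives 14.9 and 16.8 points, exact (Clopper-Pearson) about 16.2 to 16.8 and 18.7, and continuity-corrected Wald 17.2 and 19.6. The stated figures are therefore plain Wald half-widths with a design effect of 1.

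**Step 2: allow for groups.** The variance is multiplied by 1 + (m − 1) × ICC = 1 + 9 × ICC, and the half-width by its square root.

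| Assumed ICC | Design effect | Effective n (30 / design effect) | Half-width at 75% | at 70% | at 50% |
|---|---|---|---|---|---|
| 0 | 1.00 | 30.0 | 15.5 | 16.4 | 17.9 |
| 0.02 | 1.18 | 25.4 | 16.8 | 17.8 | 19.4 |
| 0.05 | 1.45 | 20.7 | 18.7 | 19.7 | 21.5 |
| 0.10 | 1.90 | 15.8 | 21.4 | 22.6 | 24.7 |

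**Step 3: compare with the worst-case figure.** At p = 0.50 any positive ICC takes the half-width above 17.9 points. At p = 0.75 the ICC that gives 17.9 solves 1 + 9 × ICC = 0.25/0.1875 = 1.333, so ICC = 0.333/9 = 0.037.

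**Step 4: would another interval formula cure it?** Take each group's count as beta-binomial (10 members, independent groups) with a true rate of 75%, and compute the coverage of nominal 95% intervals that ignore group. At ICC 0.05 and 0.10, Wald covers about 88% and 82%, and Wilson about 92% and 88%. Wilson does better at this rate, but neither reaches 95%.

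**The case against.** The case against is substantial, and much of it stands.

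- **The figures are not miscalculated.** A reader might infer an arithmetic error. There is none, as Step 1 shows. The label on 17.9 also has its ordinary meaning: 50% is the rate at which binomial variance is largest. The phrase needs qualifying, not withdrawing.
- **The evidence for dependence is qualitative.** The pilot remark concerns groups of 5 and reports no measured correlation, and the larger groups were meant as a buffer. Reminders and payment are directed at each participant, which favours independence. This limits what can be said about size, but it does not restore independence as a safe assumption.
- **No ICC can be taken from the article.** A reader might infer from the table that about 19 to 21 points is the correct half-width at 75%. The article does not support that; at an ICC of 0.02 the loss is only 1.3 points (16.8 − 15.5).
- **The scope is narrow.** Private writing and follow-up assessments are completed individually, so the stated precision is much less open to question there. A reader might extend the point to acceptability, but that is a mean on a 0 to 4 scale, and half-widths for a completion rate say nothing about it. Group cohesion is not a primary outcome.
- **The groups differ by design.** Two are age-specific and one is mixed, so treating them as random draws from one population is an approximation. A pooled proportion that is explicitly conditional on these three groups is defensible.
- **An analysis plan not shown may handle clustering in the final intervals, and the article already intends to explore engagement by group composition.** Silence about the interval method is therefore no fault. But a later analysis plan would not change the planning precision stated in the article as the reason for 30 participants.
- **No decision turns on it.** The success criteria are point thresholds, and the quantitative analyses are declared exploratory.

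**Conclusion.** The point holds for the two group-discussion criteria and for the planning statement. The 15.5 and 17.9 points are correct for 30 independent responses. For outcomes produced within three interacting groups of 10, the article's own text makes positive correlation plausible, and the stated precision is then too favourable. The direction follows from any positive ICC. The size rests on the assumed ICC and on the exchangeable-groups model behind 1 + 9 × ICC: at 75% the half-width rises by 1.3 points at ICC 0.02, 3.2 at 0.05 (18.7 − 15.5) and 5.9 at 0.10 (21.4 − 15.5).

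A reader might conclude that the sample size is inadequate or that the feasibility verdict is unsafe. The article supports neither: the thresholds apply to observed proportions, and the other completion criteria concern individual tasks. I grade this minor to moderate.

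**What to change.** **Participants (sample-size paragraph).** State that 15.5 and 17.9 points assume independent responses and apply to the individually completed tasks. Add half-widths for the two discussion criteria over a stated range of assumed ICCs, such as the table above, and say that the ICC is an assumption. Qualify the worst-case wording as referring to a 50% rate under independence.

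**Statistical Analysis.** Report discussion completion for each group (x/10) beside the pooled proportion. Either inflate the pooled 95% interval for an assumed ICC or label it conditional on these three groups. Do not try to estimate the ICC from the data: three groups are too few. An interval built from group-level results would have only 2 degrees of freedom (t = 4.30 instead of 1.96) and a half-width of about 34 points at 75% even with an ICC of zero, which is too wide to be useful.

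**Cost.** A few sentences and a small amount of analysis code. No new data are needed, no threshold changes, and enrolment, already complete, is untouched. The only downside is a slightly less favourable precision statement.
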